### Statistical considerations

Statistical analysis will be carried out using IBM SPSS Statistics 21. Radiological measurements will be registered as a continuous variable at ratio. The average progression rate per year will be analyzed using data of all patients. The progression rate per year, defined as increase in size per tumor, using RECIST criteria, with the associated range and confidence interval, will be registered as the primary outcome. The QLQ-C30 questionnaire results in a score to classify the quality of life. This score will be registered as discrete data at ratio scale. If a score cannot be rewarded, the data of the questionnaire will be regarded as missing data. If a score is missing, but later registered scores are available, the later scores will be used in assessment of the quality of life. The overall quality of life will be calculated using data of all patients at the end of follow-up. The median value will be extracted with the associated range.

The possible influence of patient and tumor related factors on the progression rate and the quality of life are analyzed using the Kaplan-Meier method and univariable Cox-regression. Associations between variables will be explored by Chi-square analysis. Multivariate analysis will be performed if possible by means of Cox-regression. Those factors which prove to have statistical significance in univariate analyses, will be included in the multivariate analysis. The considerations for treatment will be categorized and analysis will show the occurrence of specific considerations.

The interim analysis of both primary and secondary parameters will be done after one year of follow-up on 20 patients. The analyses will be the same as described above and will be performed by the principal investigator. For all analyses, two-sided *P <* 0.050 is considered statistically significant.

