**Design and methods:**

GRAFITI is a nationwide, multicenter, prospective registration trial. All patients with extra-abdominal or abdominal wall aggressive fibromatosis are eligible for inclusion in the study. Main exclusion criteria are: history of familiar adenomatous polyposis, severe pain, functional impairment, life/limb threating situations in case of progressive disease. Patients included in the study will be treated with a watchful waiting policy during a period of 5 years. Imaging studies with ultrasound and magnetic resonance imaging scan will be performed during follow-up to monitor possible growth: the first years every 3 months, the second year twice and the yearly. In addition patients will be asked to complete a quality of life questionnaire on specific follow-up moments. The primary endpoint is the rate of progression per year, defined by the Response Evaluation Criteria In Solid Tumors (RECIST). Secondary endpoints are quality of life and the rate of influence on tumor progression for several factors, such as CTNNB1-mutations, age and localization.

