### Treatment

Treatment of aggressive fibromatosis classically involves surgery, combined with radiotherapy on indication. Literature on the effects of surgery and radiotherapy on the rate of recurrence is conflicting [17–19]. While these effects are still being questioned, treatment policies have recently turned towards a more conservative approach. Nowadays, a watchful waiting approach is being advocated by various authors and is currently the standard in European care [20–25]. Retrospective studies showed that progression usually occurs within 2 years of diagnosis. Fiore et al. [22] reported a median time till progression of 14 months, with 89 % of progression observed within 2 years, while Salas et al. [18] described a median time till progression of 20 months. In addition, these studies have also reported spontaneous regression in up to 18.5 % of the patients [18, 22].

The ability to predict tumor behavior would enable tailoring individual patient treatment. Little is known about tumor growth. Available literature is dated and descriptive, without objective measurements [16].

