### Primary objective

The primary objective is to assess tumor progression in terms of objectifying and monitoring growth during watchful waiting policy as an initial treatment. Ultrasound and MRI imaging will be used to determine tumor size. Tumor behavior will be scored using RECIST. Primary endpoint is the rate of progression per year, which will be measured after 5 years of follow-up.

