### Sample size

Based on the incidence of sporadic aggressive fibromatosis and tumor localization, we expect to include 20 patients annually, we aim to include 100 patients in 5 years. Loss to follow-up or death is not to be expected. Under the most adverse conditions, a progression rate of 50 % would result in a 95 % confidence interval (95 % CI) of 40–60 %. A progression rate of 25 % would result in a 95 % CI of 18–34 %. We consider the presented 95 % CI to be acceptable for the study.

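### The primary outcome is defined as an average yearly increase in tumour size, but the sample size gives precision for a proportion of patients who progress, so the stated confidence intervals do not belong to it

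*Protocol article*

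**What the plan says.** The protocol article describes the primary outcome in four places.

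- **Abstract (Design and methods):** a yearly rate of progression, with progression defined by RECIST.
- **Primary objective:** "Primary endpoint is the rate of progression per year, which will be measured after 5 years of follow-up". Tumour behaviour is to be scored by RECIST.
- **Statistical considerations:** "Radiological measurements will be registered as a continuous variable at ratio". Then: "The average progression rate per year will be analyzed using data of all patients". The primary outcome itself is "The progression rate per year, defined as increase in size per tumor, using RECIST criteria", to be reported with a range and a CI.
- **Sample size:** "Under the most adverse conditions, a progression rate of" 50% is given a 95% CI of 40–60%, and a rate of 25% a CI of 18–34%, for 100 patients. No time point is attached, and no loss to follow-up is expected.

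The Statistical considerations section then studies factors influencing the progression rate by Kaplan-Meier and Cox regression. Both need progression to be an event with a time.

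**The concern.** The same term stands for a continuous quantity in the definition of the primary outcome, a proportion of patients in the sample-size section, and an event in the factor analyses. Two things follow.

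First, the only statement of precision, which the sponsor declares acceptable, concerns a proportion. The precision of a mean growth rate depends on a standard deviation, and the article gives none.

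Second, the Discussion says the study should help determine who can safely be managed by watchful waiting. That calls for the chance and timing of progression. A mean of signed size changes lets regressing tumours offset progressing ones, and one yearly figure over 5 years does not show when progression happens. The Treatment section itself cites a retrospective series with 89% "of progression observed within 2 years".

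**Working it through.** **1. Reproducing the stated intervals.** Inputs from Sample size: n = 100, p = 0.50 or 0.25. Wilson interval with z = 1.96:

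centre = (p + z²/2n)/(1 + z²/n); half-width = z·√(p(1-p)/n + z²/4n²)/(1 + z²/n)

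- p = 0.50: 0.500 ± 0.0962, or 40.4–59.6%. The plan says 40–60%.
- p = 0.25: 0.2592 ± 0.0838, or 17.5–34.3%. The plan says 18–34%; the unrounded lower limit is 17.55.

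For the 25% case the Wald interval (16.5–33.5%) and the Clopper-Pearson interval (16.9–34.7%) do not match. The arithmetic is right, and it describes a simple binomial proportion.

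**2. Precision of the outcome as defined.** For a mean, half-width = t(0.975, 99) × SD/√100 = 1.984 × SD/10. The documents give no SD, so these values are assumptions, in percentage points per year:

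| Assumed SD | 95% half-width |
|---|---|
| 10 | 2.0 |
| 20 | 4.0 |
| 30 | 6.0 |
| 40 | 7.9 |

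None of these can be read from the 40–60% or 18–34% intervals.

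**3. Reading it as an event rate per year.** The sample-size proportion still lacks a time point, and that matters. If 50% is the 5-year figure, the average is 50/5 = 10 points per year. If 50% were an annual risk, constant over 5 years (an assumption), the 5-year figure would be 1 - 0.5⁵ = 96.9%.

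**4. Can averaging mask progression?** Document inputs: regression in up to 18.5% (Treatment; the Discussion's 5 of 27 is the same share) and progression of 25% or 50% (Sample size). Assumed: regressors -30%, stable tumours 0%, progressors +20% to +40%. These are total changes, not annual ones. Mean = p × growth - 0.185 × 30:

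| Progressing | Growth | Mean change | 95% half-width, n = 100 |
|---|---|---|---|
| 25% | +20% | 5.0 - 5.55 = -0.55% | 3.24 |
| 25% | +30% | 7.5 - 5.55 = +1.95% | 3.91 |
| 25% | +40% | 10.0 - 5.55 = +4.45% | 4.64 |
| 50% | +20% | 10.0 - 5.55 = +4.45% | 3.69 |
| 50% | +40% | 20.0 - 5.55 = +14.45% | 5.46 |

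In the three 25% rows the interval includes zero although a quarter of patients progressed. In the 50% rows it does not.

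**5. Timing.** Assume 50% progress by 5 years and the cited 89% applies. Years 1–2: 0.89 × 50/2 = 22.3 points per year. Years 3–5: 0.11 × 50/3 = 1.8 points per year. The 5-year average of 10 describes neither period.

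**The case against.** The strongest reply is that the analysis section is only loosely worded. It mentions RECIST, the Abstract and Primary objective tie progression to RECIST, and the Kaplan-Meier and Cox analyses treat progression as an event. On that reading a RECIST event rate was meant throughout. That is plausible, but the text gives an explicit definition by size increase, an average and continuous data. An ambiguous primary outcome with precision stated for only one reading still has to be settled. Because the article states the definition, this is not a detail left to a fuller document.

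Several stronger readings are tempting and not supported:

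- **That the outcome is measured only once.** The Primary objective says after 5 years of follow-up; Table 1 schedules imaging at nine follow-up visits, six of them by month 24.
- **That a yearly average assumes a constant rate and so contradicts the 89%.** An average summarises and does not assume constancy. The 89% comes from one retrospective series.
- **That the trial will report growth near zero.** This depends on assumed size changes and on the maximum cited regression share; the 50% scenario gives +4.5% or more. The range is also to be reported, and would show tumours moving in both directions.
- **That 100 patients is too few, or the interval arithmetic wrong.** Neither is shown. The number follows expected accrual of 20 a year, and the intervals reproduce.

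It is also fair that this is a single-arm observational study with no test on the primary outcome, and that its interim safety criterion rests on the share still under watchful waiting at 1 year, not on mean growth.

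**Conclusion.** The point holds as a conflict between definition and stated precision. The sample-size intervals are binomial intervals for 100 patients; the primary outcome in the analysis section is an average size increase per year, whose precision is unknown (half-width 2.0 to 7.9 points for assumed SDs of 10 to 40). This part rests on the text and on reproducing the plan's own figures.

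The masking and timing arguments show what is at stake, and they depend on assumptions. A mean can hide progression when some tumours regress, but need not. The contrast of 22.3 against 1.8 points per year is an illustration from one cited series and an assumed 5-year risk. Since this is the primary outcome, the definition should be settled before analysis.

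**What to change.** Use one definition in the Abstract, Primary objective, Sample size and Statistical considerations: the cumulative incidence of first RECIST progression at 5 years with its 95% CI, also reported at 1 and 2 years. Delete the clause defining the progression rate as size increase per tumour, and make annual change in size a secondary outcome.

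State how a switch to active treatment before progression is counted in the analysis, as censoring or as a competing event. The article keeps such patients on study for the questionnaires and does not say the same of imaging.

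Attach the 5-year time point to the 50% and 25% scenarios. Add that their intervals hold exactly only with complete follow-up, and would be somewhat wider if patients are censored or switch before progressing.

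The cost is wording. The scans are already in Table 1, and no new data or patients are needed.

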### Secondary objectives

The secondary objective is to investigate the effect of treatment on the quality of life. During the study period, patients will be asked to complete the EORTC QLQ-C30 questionnaire five times: at inclusion and after 6,12,24 and 60 months. After a switch to active treatment, patients will remain on-study for the questionnaires. The scores will be evaluated and related to treatment policy.

Other objectives are to analyze the value of clinicopathological factors, including CTNNB1-gene mutation, in predicting progression. The reasons and considerations for active treatment will be analyzed in relation to the applicability of a watchful waiting policy.

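### Quality of life, a repeated score, is assigned to Kaplan-Meier and Cox regression with no event defined, and no stated model relates it to treatment policy

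*Protocol article*

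**What the plan says.** The protocol article, Secondary objectives, sets the aim: "The secondary objective is to investigate the effect of treatment on the quality of life". The QLQ-C30 is completed "five times: at inclusion and after 6,12,24 and 60 months", which agrees with Table 1. Collection does not stop at a change of policy: "After a switch to active treatment, patients will remain on-study for the questionnaires". The section closes with an intention but names no method: "The scores will be evaluated and related to treatment policy".

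Statistical considerations then deal with quality of life in three steps:
- The variable: "This score will be registered as discrete data at ratio scale".
- The summary: "The overall quality of life will be calculated using data of all patients at the end of follow-up", followed by "The median value will be extracted with the associated range".
- The inferential analysis: the influence of patient and tumour characteristics on "the progression rate and the quality of life are analyzed using the Kaplan-Meier method and univariable Cox-regression".

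The same section names Chi-square for associations between variables, Cox regression for the multivariable step, and an interim look at primary and secondary parameters after one year in 20 patients.

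**The concern.** Kaplan-Meier and Cox regression need an event and a time from a defined origin to that event. Progression can supply both. A QLQ-C30 score on a fixed calendar supplies neither until someone defines what counts as deterioration, from when it is counted, and whether it must be confirmed. An analyst following the text would have to choose a cut-off, possibly with the data in view.

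The second gap concerns the objective. It asks how treatment relates to quality of life, and the questionnaires continue after a switch so that this can be studied. The explanatory variables named for the quality-of-life models, however, are patient and tumour characteristics, not treatment policy. A median over everyone shows neither change from baseline nor a difference between patients who stayed on watchful waiting and those who switched.

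**Working it through.** The plan states no quality-of-life figure to reproduce. Its only precision figures (Sample size: 40–60% at a 50% rate and 18–34% at 25%, n = 100) concern progression. A Wilson interval gives 40.4–59.6% and 17.5–34.3%, so they stand, but they do not bear on this point.

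**Step 1: what each method needs, against what is given.**

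| Needed | Given in the protocol article |
|---|---|
| Event (Kaplan-Meier, Cox) | None for quality of life; a numeric score only |
| Time origin | None stated for quality of life |
| Event time | Observable only at months 6, 12, 24 and 60, so interval-censored |
| Treatment policy as explanatory variable | Intended in Secondary objectives; in no model in Statistical considerations |
| Change from baseline | Baseline score collected; used in no stated analysis |

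The gaps between questionnaires are 6, 6, 12 and 60 − 24 = 36 months. The timing of any deterioration would therefore be coarse. A patient who switches late may have a last pre-switch score almost three years old.

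**Step 2: how far a Cox result would depend on the missing definition.** Assumed, not from the documents: SD 20, within-patient correlation ρ = 0.5 or 0.7, normal scores, no true change. The difference between two visits has SD = 20 × √(2(1 − ρ)), which is 20.0 at ρ = 0.5 and 15.5 at ρ = 0.7. The chance of a drop of at least c at one visit is 1 − Φ(c/SD). For c = 10 and ρ = 0.5 this is 1 − Φ(0.5) = 31%. The chance of such a drop at any of the four later visits was simulated (200,000 patients):

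| Drop of at least | ρ = 0.5 | ρ = 0.7 |
|---|---|---|
| 5 points | 71% | 68% |
| 10 points | 60% | 53% |
| 20 points | 37% | 25% |

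The number of events thus varies about two- to threefold with a cut-off that the plan does not give, even when nothing has changed.

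**Step 3: what the pooled median can show.** Further assumptions: n = 100, mean 70, ρ = 0.5, a shift of −8 points after switching, switch times spread evenly over months 3 to 48, and switching unrelated to the score. If the median is taken at month 60, it should move by about (share switched) × 8: 0.25 × 8 = 2 points or 0.50 × 8 = 4 points. Simulation (2,000 runs) gives 68.1 and 66.0, with a sampling SD of about 2.5 to 2.6. The shift is of the order of the sampling error and cannot be attributed to the switch. On the same data, a within-patient regression with visit effects and a time-varying switch indicator detects the shift in about 70% and 88% of runs. Its false-positive rate in these simulations was 6.9% and 5.8%, slightly above the nominal 5%, so the power figures are a little generous.

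**The case against.** Several points on the other side have force.

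- **Kaplan-Meier and Cox are not barred from quality of life.** Time to deterioration is a legitimate outcome, and a condensed article may leave its definition to a fuller document. A reader might infer that these methods can never apply. That goes too far. What stands is that the text assigns them to something it describes only as a numeric score, so this is a stated method that does not fit, not merely a missing detail.
- **The median may not be restricted to month 60.** A reader might infer that only one of five scores is used. The sentence is ambiguous: the end of follow-up may be when the calculation is made, not which score enters. The rule that later scores serve when one is missing, and the one-year interim analysis, both suggest that other scores have some role.
- **The median is not the only other analysis named.** Chi-square tests and the interim analysis are there too, though neither models a repeated score or treatment policy.
- **Pooling is not an error in itself.** The study evaluates watchful waiting as the initial approach, and a median over all patients describes quality of life under that strategy, whatever follows. It is sound description but does not answer the question about treatment.
- **Confounding by the reasons for switching is inherent in the design.** No model removes it, and the plan already has those reasons documented.

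**Conclusion.** The point holds. As written, the time-to-event methods do not fit the quality-of-life outcome, and the stated objective of relating scores to treatment policy has no matching model. Both conclusions rest on the text alone.

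A reader might infer that the secondary objective is beyond reach. The documents do not support that: the scores are collected before and after a switch, and the intention to relate them to policy is stated. The method is what is lacking.

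The size is illustrative. The figures depend on an assumed SD, correlation and switch effect, and on switching that is unrelated to the score. Real switching may follow growth. The gain from baseline adjustment is sometimes put as a cut in residual variance of r² (0.5² = 25%, 0.7² = 49%). That is also assumption-based, and it measures precision, not this fault.

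Severity is moderate. Quality of life is a secondary endpoint in an observational study, and the primary endpoint, sample size and data collection are unaffected.

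**What to change.** In Statistical considerations:

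1. Restrict Kaplan-Meier and Cox regression to progression.
2. Analyse the QLQ-C30 scores at months 6, 12, 24 and 60 with a linear mixed model for repeated measures. Include the baseline score, visit, patient and tumour factors, and a time-varying indicator of having switched to active treatment.
3. Report the switch contrast as a non-randomised association. Note that no questionnaire falls between months 24 and 60, so the last pre-switch score may be old.
4. Keep the overall median and range as description only, and say which visit or visits it covers.
5. If a time-to-event analysis of quality of life is kept, define the deterioration event and its origin in advance, and allow for interval-censored timing.

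The cost is a change of wording and slightly more analysis work. No visits, questionnaires or patients are added.

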## Discussion

During the last decade, there has been a shift in treatment strategy for aggressive fibromatosis from aggressive to conservative modalities. A watchful waiting policy is currently advised for extra-abdominal and abdominal wall aggressive fibromatosis [25]. Research validating the efficacy and applicability of a watchful waiting policy is limited. Mitchell et al. were the first to describe a stable phase for aggressive fibromatosis [5]. In a retrospective study of 17 patients under medical observation, all experienced at least one period of stable disease for over 6 months. A larger study by Fiore et al. evaluated 142 patients with primary and recurrent aggressive fibromatosis, treated with initial conservative treatment retrospectively [22]. Approximately 50 % of the patients did not have tumor progression after 1 year. Spontaneous regression has been reported by Salas et al. [18]. In a retrospective study analyzing 426 patients with aggressive fibromatosis, 27 patients were treated with a watchful waiting policy. Five of these patients had spontaneous remission, 16 patients stable disease and 6 patients had progressive disease. The median time to progression was 19.7 months. A recent study by [name] et al. reported 216 patients with primary extra-abdominal (*n =* 188) and intra-abdominal (*n =* 28) disease undergoing a diversity of treatments [24]. Initial wait-and-see policy was applied in 70 patients (60 extra-abdominal) and continued till the end of follow-up in 60 %. Progression occurred in 16 of the 70 patients, mostly treated with systemic modalities. These results demonstrate the potential safety of a watchful waiting policy.

Current knowledge on predictive factors is mostly based on surgical cohorts. Age, tumor localization and tumor size have been reported as predictive factors for the risk of recurrence following surgery. A nomogram was proposed by Crago et al. [27] using all these factors in a postoperative setting.

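### Chi-square is the only method named for associations between variables, although age and tumour size are continuous; a rank test or correlation would keep power at almost no cost (minor)

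*Protocol article*

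**What the plan says.** All the analysis wording is in the protocol article under Statistical considerations.

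- Associations between variables: "Associations between variables will be explored by Chi-square analysis". No other method is named for this step.
- Influence of patient and tumour factors on progression and quality of life: these "are analyzed using the Kaplan-Meier method and univariable Cox-regression".
- Multivariable step: "Multivariate analysis will be performed if possible by means of Cox-regression". Entry rule: "Those factors which prove to have statistical significance in univariate analyses, will be included in the multivariate analysis".
- Scale of tumour measurements: "Radiological measurements will be registered as a continuous variable at ratio".

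The continuous factors are named elsewhere. The abstract (Design and methods) lists factors "such as CTNNB1-mutations, age and localization". The Discussion states "Age, tumor localization and tumor size have been reported as predictive factors for the risk of recurrence following surgery", adds mutation status, and then says that the study was set up to examine these factors under watchful waiting. No section says that age or size will be grouped, and none gives a cut-point.

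**The concern.** Chi-square compares counts in categories. A variable such as age in years or maximum tumour diameter must be cut into groups before the test can be applied. Followed as written, the association step therefore turns measurements recorded on a continuous scale into a few classes. With at most 100 patients, the information lost can hide a real association, for example between age and mutation type or between age and tumour size. Such associations help a reader judge whether an apparent predictor stands in for another one. A test suited to continuous data is available in the software the article names, so the loss buys nothing.

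**Working it through.** **The article's own figures.** The only statistical figures are the two confidence intervals under Sample size. With n = 100 and z = 1.96, the Wilson interval is (p + z²/2n ± z·√[p(1−p)/n + z²/4n²]) / (1 + z²/n). For p = 0.50 this gives 40.4% to 59.6%, and for p = 0.25 it gives 17.5% to 34.3%. Both match the stated 40–60% and 18–34% (the lower limit for 25% is 17.55% before rounding). No power, effect size or cut-point is given for the factor analyses, so every effect size below is an assumption.

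**Inputs from the article.** n = 100 and progression rates of 25% and 50%, hence about 25 or 50 events (Sample size); two-sided 5% level (Statistical considerations).

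**Association 1: age against a mutation.** Assumed: mutation in 30 of 100 patients, a 0.6 SD difference in age, normal distribution.

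- Signal on the uncut scale: 0.6 × √(30 × 70/100) = 0.6 × 4.583 = 2.750.
- Rank test (efficiency 3/π = 0.955): 2.750 × √0.955 = 2.687. Power = Φ(2.687 − 1.96) = Φ(0.727) = 77%.
- Chi-square on a median split (efficiency 2/π = 0.637): 2.750 × √0.637 = 2.194. Power = Φ(2.194 − 1.96) = Φ(0.234) = 59%.
- Simulation of the same setting: about 75% against 58%, a loss of about 17 points.

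**Association 2: two continuous factors, such as age and size.** Assumed: bivariate normal, correlation 0.3.

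- Spearman: the rank correlation is (6/π)·arcsin(0.15) = 0.288. Power = Φ(0.296 × √(97/1.06) − 1.96) = Φ(0.87) = 81%, where 0.296 is the Fisher transform of 0.288.
- Chi-square after both are split at the median: the correlation of the two binary variables is (2/π)·arcsin(0.3) = 0.194. Power = Φ(0.194 × √100 − 1.96) = Φ(−0.02) = 49%.
- Simulation: about 82% against 56%, a loss of about 26 points. The simulated chi-square figure exceeds 49% because, with all margins equal to 50, the uncorrected statistic takes only the values 0.16k², where k is the cell count minus 25. It first passes 3.84 at k = 5. The variance of the cell count is 50⁴/(100² × 99) = 6.31 (SD 2.51), so the true level is about 2 × [1 − Φ(4.5/2.51)] = 7%. The 56% therefore slightly flatters chi-square.

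**Progression analysis, for comparison only.** Power for Cox is Φ(√(events × efficiency) × ln HR − 1.96), with efficiency 1 if uncut and 0.637 if split at the median. Assumed hazard ratio 1.5 per SD, so ln HR = 0.405.

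| Events | Uncut | Median split |
|---|---|---|
| 25 | Φ(2.03 − 1.96) = 53% | Φ(1.62 − 1.96) = 37% |
| 50 | Φ(2.87 − 1.96) = 82% | Φ(2.29 − 1.96) = 63% |

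At other assumed hazard ratios the pairs are 26% and 18% (1.3, 25 events) and 98% and 88% (1.75, 50 events). The right-hand column applies only if the factors are split before they enter Cox, which the article does not say.

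**The case against.** The strongest reply is that the association step is exploratory and decides nothing. Entry to the multivariable model follows from the univariate analyses of progression, not from chi-square, and factor-against-factor comparisons are not a listed objective. Several of the factors are categorical (mutation status, localization, primary or recurrent disease), and chi-square suits those. This stands, and it is why the point is minor. It does not remove the mismatch for age and size.

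A reader might infer more: that the plan forces age and tumour size into categories throughout, and so weakens or distorts the search for predictors of progression. The article does not support that. The sentence that names Kaplan-Meier also names univariable Cox regression, and multivariable Cox follows; both accept uncut values. That a factor grouped for a curve would also be grouped in Cox is a guess about practice. Cut-points and the form in which a covariate enters a model are details that a journal article may leave to the full protocol or analysis plan, so their absence is not an error.

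A reader might also infer inflated false positives. Choosing the best of seven cut-points from the data would raise a 5% error rate to about 21%, and searching every cut between the 20th and 80th percentiles would raise it to 31–32%. The article announces no such search. A median cut fixed in advance stays at about 5%.

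**Conclusion.** The point holds in a limited form, at minor severity. The article names one method for associations, and that method does not suit two continuous factors it wants to evaluate. Under the assumed effects the cost is about 17 points of power for a continuous variable against a binary one, and about 26 points for two continuous variables. These sizes rest on n = 100, median splits, normal distributions, a 30% mutation frequency with a 0.6 SD difference, and a correlation of 0.3. None of these except n comes from the article, and other effects would give other losses. The direction does not depend on the exact values. No defect is shown in the analysis of progression, where any loss of power or rise in false positives would depend on choices the article does not make.

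**What to change.** Under Statistical considerations:

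1. Explore associations that involve a continuous variable with a rank test (continuous against categorical) or Spearman correlation (two continuous variables). Keep chi-square for pairs of categorical variables, with Fisher's exact test where cells are sparse.
2. State that age and tumour size enter the univariable and multivariable Cox models uncut, and that this univariable Cox result decides entry to the multivariable model. Use Kaplan-Meier groupings of these two for display only. This closes the readings discussed above and leaves no doubt about which univariate result counts.

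The cost is a few sentences. The methods are standard and available in the named software, and neither data collection nor patient care changes. The one drawback is that a hazard ratio per unit is slightly harder to present than two curves.
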